The main aims of the study are to evaluate for the first time the long-term adherence to e-cigarette smoking and the efficacy of e-cigarettes in reducing and/or quitting traditional cigarette smoking. As secondary aims, the study will also evaluate the long-term safety (in terms of smoking-related serious diseases requiring hospitalization) of e-cigarette smoking, comparing its health effects with those of traditional cigarette smoking and mixed electronic and traditional cigarette smoking. We will evaluate over a 5-year follow-up the number of smoking-related hospitalizations, the self-reported quality of life, and the reported adverse events according to current and past smoking habit.

The present paper describes the research protocol of the project, which is currently on course (NCT01785537).

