### Secondary outcomes

1. Adherence to e-cigarette smoking: number of months of continued e-cigarette smoking in groups EC and Mixed.

2. Traditional and electronic smoking (overall smoking) cessation: percentage of subjects in all groups reporting sustained smoking abstinence from both traditional and electronic cigarette smoking at 6, 12, 24, 36 and 60 months. Smoking abstinence is defined as complete abstinence from tobacco or electronic smoking (not even a puff) for the 30 days period prior to the visit.

3. Time to hospital admission for one of the followings: cardiovascular diseases, chronic obstructive pulmonary diseases, cancer of the lung, esophagus, larynx, oral cavity, bladder, pancreas, kidney, stomach, cervix, and myeloid leukemia. Repeated admissions of the same subject will be counted once and the subject will be censored at the date of the first admission.

4. Rate of subjects with smoking-related hospitalizations: percentage at 1, 2, 3 and 5 years of subjects who had a hospital admission for one of the followings: cardiovascular diseases, chronic obstructive pulmonary diseases, cancer of the lung, esophagus, larynx, oral cavity, bladder, pancreas, kidney, stomach, cervix, and myeloid leukemia. Repeated admissions of the same subject will be counted once.

5. Number of smoking-related hospitalizations: mean number at 1, 2, 3 and 5 years of hospital admissions for one of the followings: cardiovascular diseases, chronic obstructive pulmonary diseases, cancer of the lung, esophagus, larynx, oral cavity, bladder, pancreas, kidney, stomach, cervix, and myeloid leukemia. Each admissions of the same subject will be counted.

6. Number of hospitalizations for cardiovascular diseases: mean number at 3 and 5 years of hospital admissions for cardiovascular diseases. Each admissions of the same subject will be counted.

7. Number of hospitalizations for smoking-related cancers: mean number at 3 and 5 years of hospital admissions for cancer of the lung, esophagus, larynx, oral cavity, bladder, pancreas, kidney, stomach, cervix, and myeloid leukemia. Each admissions of the same subject will be counted.

8. Self-reported quality of life: average quality of life according to EuroQoL EQ-5DL at 6, 12, 24 and 36 months. The analysis of quality of life will follow the technical specifications recommended by the EuroQol group [29].

9. Reported side effects at 6, 12, 24, 36 and 60 months.

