### Data analysis

All data will be collected and initially handled by the Coordinating unit, which is responsible for privacy regulations and maintains the property.

At each time-point, the differences in the rates of traditional smoking cessation (or other categorical outcomes such as adverse events) across groups will be first examined using Fisher’s exact test. Cox proportional hazards analysis will be used to calculate the adjusted relative hazards of traditional smoking cessation (and smoking-related hospitalization) by each variable. Stochastic level of entry into the model will be set at 0.10, with age, gender, and smoking groups forced to entry, and multicollinearity, interactions with time to event and higher-power terms will be explored for all variables in the final model. A minimum events-to-variable ratio of 10 will be maintained in multivariate modeling to avoid overfitting, and Schoenfeld’s test will be performed to check the validity of proportional hazards assumption. Kaplan-Meier survival analysis will also be used to examine the association between hospitalization and smoking group. The validity of constant incidence ratios over the follow-up will be checked using Nelson-Aalen cumulative hazard estimates.

Multiple linear regression will be used to investigate the predictors of the difference in the number of traditional cigarettes smoked between baseline and each time-point of follow-up. Additional multivariate models such as mixed-effect logistic models will be explored for both the primary and secondary outcomes to account for repeated observations and the potential distortions of the variability in the exposure to traditional cigarette smoking by the participants in groups EC and Mixed (for which also stratification will be considered) [31]. In all mixed models, the cluster variables will be participant’s id, nicotine level of the electronic and traditional cigarette and exposure to past traditional cigarette smoking. We will assume and independent correlation structure for all clusters, but we will also repeat all models setting an exchangeable correlation structure.

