The prevalence of e-cigarette smoking compliance (secondary outcome n. 1) will similarly be derived at 6, 12, 24, 36 and 60 months. However, with the exception of the 6-months cut-off (which will probably include the vast majority of participants), the crude estimates of adherence for the following time-points would most probably be underestimated, as several participants who are still adherent will be excluded because they will not be followed up to the cut-off point. Therefore, adjusted estimates of adherence for each follow-up point will be calculated using the Nelson-Aalen method for censoring, which assigns censored observations according to the corresponding period of failure incidence [32].

A p-value of <0.05 will be considered significant for all analyses, which will be performed using STATA statistical software, version 11.1 (Stata Corporation, College Station, TX, USA, 2007).

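### The Nelson-Aalen method named for adherence gives a cumulative hazard of stopping, not the proportion still using e-cigarettes, and no conversion is stated

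*Protocol article*

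**What the plan says.** Under Secondary outcomes, the protocol article defines adherence as a duration: "number of months of continued e-cigarette smoking in groups EC and Mixed". Under Data analysis the same outcome becomes a proportion at fixed times: "The prevalence of e-cigarette smoking compliance (secondary outcome n. 1) will similarly be derived at 6, 12, 24, 36 and 60 months". The authors expect loss to follow-up to distort the simple proportion, in that "the crude estimates of adherence for the following time-points would most probably be underestimated". Their remedy is that "adjusted estimates of adherence for each follow-up point will be calculated using the Nelson-Aalen method for censoring", a method they describe as one "which assigns censored observations according to the corresponding period of failure incidence".

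The same section uses two survival methods elsewhere. The constancy of incidence ratios over follow-up "will be checked using Nelson-Aalen cumulative hazard estimates". For hospital admissions, "Kaplan-Meier survival analysis will also be used to examine the association between hospitalization and smoking group". Kaplan-Meier is not mentioned for adherence.

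Adherence is formally secondary outcome 1, but the Background puts it first among the aims: "The main aims of the study are to evaluate for the first time the long-term adherence to e-cigarette smoking".

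**The concern.** The quantity wanted is the share of EC and Mixed participants still using e-cigarettes at each of five times, allowing for censoring. Nelson-Aalen adds up the observed stopping fractions over time. The sum starts at 0, rises, and has no upper limit of 1, so it is not a share of participants. The article uses the method for what it does estimate when it checks incidence, and then names it for a different quantity without saying how one becomes the other.

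This is a method that the article states, not a detail that it leaves out. An analyst who follows the text has at least two ways to turn H into an adherence figure, exp(-H) and 1 - H. They err in opposite directions, and the size of the error depends on how finely stopping is dated. At stake is the adherence figure at each time point, most of all at 60 months, for an outcome that the Background counts among the main aims.

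**Working it through.** The article states no adherence figure, so there is none to reproduce. The check compares the estimators on the same data.

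**Inputs from the protocol article.** Questionnaires at 6, 12, 24, 36 and 60 months; at least 500 participants per group; 20% withdrawals or dropouts.

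**Assumed.** True 60-month adherence of 80, 60, 50, 40 or 20%, with a constant rate of stopping. Stopping is dated either by month or only at the questionnaires.

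**Formulas.** With d the number stopping and n the number at risk at each recorded time:

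- Kaplan-Meier: S = product of (1 - d/n)
- Nelson-Aalen: H = sum of d/n
- Candidate conversions: exp(-H) and 1 - H

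Because exp(-x) is never below 1 - x, exp(-H) can never be below Kaplan-Meier on the same data. Because a product of terms (1 - x), with each x between 0 and 1, is never below 1 minus the sum of the x, 1 - H can never be above it.

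**One case in full (true adherence 50%).** The gaps between questionnaires are 6, 6, 12, 12 and 24 months. The fraction stopping in a gap of g months is 1 - 0.5^(g/60), which gives 0.067, 0.067, 0.129, 0.129 and 0.242.

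- Kaplan-Meier: 0.5^((6+6+12+12+24)/60) = 0.500
- H = 0.635 (sum of the unrounded fractions)
- exp(-0.635) = 0.530, which is 3.0 points too high
- 1 - 0.635 = 0.365, which is 13.5 points too low

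With monthly dating, each fraction is 1 - 0.5^(1/60) = 0.01149. Then H = 60 × 0.01149 = 0.689, exp(-H) = 0.502 and 1 - H = 0.311.

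**All cases at 60 months.** Kaplan-Meier equals the true value in every row.

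| True | H, questionnaire dating | exp(-H) | 1 - H | H, monthly dating | exp(-H) | 1 - H |
|---|---|---|---|---|---|---|
| 80% | 0.217 | 80.5% | 78.3% | 0.223 | 80.0% | 77.7% |
| 60% | 0.479 | 62.0% | 52.1% | 0.509 | 60.1% | 49.1% |
| 50% | 0.635 | 53.0% | 36.5% | 0.689 | 50.2% | 31.1% |
| 40% | 0.817 | 44.2% | 18.3% | 0.909 | 40.3% | 9.1% |
| 20% | 1.322 | 26.6% | -32.2% | 1.588 | 20.4% | -58.8% |

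The excess of exp(-H) over the truth is 0.5 to 6.6 points with questionnaire dating and at most 0.4 points with monthly dating.

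**A second pattern.** Suppose the same fraction q of remaining users stops at each of the five questionnaires. For q = 10, 20 and 30%, Kaplan-Meier is (1 - q)^5 = 59.0, 32.8 and 16.8%. H = 5q = 0.5, 1.0 and 1.5, and exp(-H) = 60.7, 36.8 and 22.3%. The excess is 1.7, 4.0 and 5.5 points, in line with the table.

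**With censoring.** The case of 50% true adherence was simulated with 500 participants, 20% lost by 60 months and 2000 runs. Kaplan-Meier averaged 50.0% under both datings. exp(-H) averaged 50.2% (monthly) and 53.0% (questionnaire). exp(-H) with the Fleming-Harrington tie correction to the hazard averaged 50.0% under both. The crude share seen to be still using, out of 500, was 39.9%, so the authors are right that some adjustment for censoring is needed.

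**The case against.** The strongest reply is that Nelson-Aalen is a valid method for right-censored data and that exp(-H) is a standard survival estimate, asymptotically equivalent to Kaplan-Meier. The authors call it a cumulative hazard in the same section, so they know what it returns. A condensed article may leave the conversion to a fuller document. The outcome is defined in months, which suggests monthly dating, and then the difference is negligible.

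Much of this stands. A reader might infer that the reported adherence will be wrong, or that H itself will be printed as a proportion. The documents do not support either: the text names adherence as the target and nowhere says that H is the figure to be reported. A reader might also infer that the method always overstates adherence. That is true only of exp(-H) without a tie correction, and it matters only if stopping is dated coarsely; 1 - H understates.

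Nor does the article's description of how censored participants are handled show that another estimator was meant. Nelson-Aalen and Kaplan-Meier use the same risk sets and the same fractions d/n, so the phrase does not separate them. The source cited for it is not at hand.

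What does not fall away is that the one method named for a proportion does not return a proportion. The outcome definition does not settle how stopping is dated either. Data come from questionnaires up to two years apart, and the questionnaire itself is not among the documents.

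**Conclusion.** The point holds as a flaw in the specification of a secondary outcome that is also listed as a main aim. The method named returns a cumulative hazard, the target is a proportion, and the step between them is missing.

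Its effect depends on two things that the article does not fix: the conversion, and how stopping is dated. It ranges from nothing of note (exp(-H), monthly dating) through a few points upward (exp(-H), questionnaire dating) to a large understatement (1 - H). The upward error falls from 6.6 points at 20% true adherence to 0.5 points at 80%. These sizes rest on assumed adherence levels and a constant stopping rate. The direction of each conversion relative to Kaplan-Meier does not depend on those assumptions.

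The sample size section does not use adherence, so its figures stand.

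**What to change.** In the adherence paragraph of Data analysis, replace Nelson-Aalen with Kaplan-Meier (or life-table) estimates of the proportion still using e-cigarettes at 6, 12, 24, 36 and 60 months, with 95% confidence intervals. This returns the wanted quantity directly and needs no conversion. In the table it equals the true 60-month value under either dating. Keep Nelson-Aalen for the check on constant incidence ratios.

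The cost is a change of wording. Kaplan-Meier is already planned for hospital admissions, and no extra data, participants or software are needed.

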### Primary outcomes

1. Traditional smoking cessation: percentage of subjects that were current (in TC and Mixed groups) or former (in EC group) smokers reporting sustained smoking abstinence from traditional cigarette smoking at 6, 12, 24, 36 and 60 months. Smoking abstinence is defined as complete abstinence from tobacco smoking (not even a puff) for the 30 days period prior to the visit.

2. Decrease in the number of traditional cigarettes smoked: average difference in self-reported number of traditional cigarettes smoked per day at baseline and 6, 12, 24, 36 and 60 months in the groups TC and Mixed.

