### Sample size estimation

The primary analyses will compare: (A) the primary outcome 1 (rate of traditional smoking sustained cessation) across the groups TC, Mixed and EC (only the subjects that were former traditional smokers); (B) the difference in the number of traditional cigarettes smoked per day between baseline and end of follow-up in groups TC and Mixed.

As regards primary analysis 1, conservatively assuming a 5-year cessation rate of 20% in the TC group, and 30% in the Mixed group (EC group most probably having a higher cessation rate), we would need 313 subjects per group to achieve a power of 80%. Given the need of multivariate modeling and an expected 20% rate of withdrawals/dropouts, 500 subjects would be required in each group.

Concerning primary analysis 2, assuming a 5-year reduction in the number of smoked traditional cigarettes of 2 ± 6 and 4 ± 6 in the Mixed group, with the same above parameters (alpha error = 0.05; beta-error = 0.20; dropout/withdrawals = 20%), we would only require 240 subjects per group.

We will thus conservatively enroll a minimum of 500 subjects in each group (EC, TC and Mixed), for a total of 1500 participants.

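### Two primary outcomes are each tested at up to five visits at an unadjusted 0.05, and no deciding visit is fixed for cessation, so the chance of a false positive primary result exceeds 5%

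*Protocol article*

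**What the plan says.** - **Outcomes.** Under Primary outcomes, outcome 1 is the percentage "reporting sustained smoking abstinence from traditional cigarette smoking at 6, 12, 24, 36 and 60 months". Outcome 2 is the change in cigarettes per day at the same five visits, in TC and Mixed only.
- **Testing.** Data analysis takes "At each time-point, the differences in the rates of traditional smoking cessation" across groups by Fisher's exact test, then fits a Cox model with smoking group forced in. Linear regression is used for "the difference in the number of traditional cigarettes smoked between baseline and each time-point of follow-up".
- **Threshold.** The same section closes with "A p-value of <0.05 will be considered significant for all analyses".
- **Primary analyses.** Sample size estimation says that analysis A compares "the primary outcome 1 (rate of traditional smoking sustained cessation) across the groups TC, Mixed and EC" (former smokers only in EC) and names no visit. Analysis B is the change from baseline to end of follow-up, TC against Mixed.
- **Sizing of A.** The calculation is for one pair at one time, "conservatively assuming a 5-year cessation rate of 20% in the TC group, and 30% in the Mixed group", from which "we would need 313 subjects per group to achieve a power of 80" per cent. The error rates and dropout are given as "alpha error = 0.05; beta-error = 0.20; dropout/withdrawals = 20" per cent.

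**The concern.** The article states its significance rule outright, and the rule covers every visit of both primary outcomes. Nothing ranks the two outcomes or divides alpha between them. For cessation, nothing says which visit or which pair of groups settles the question. A difference between Mixed and TC at 6 or 12 months that has gone by 60 months would be significant under the rule at one visit and not at another, and the text does not say which result stands. The Discussion expects the study to inform guidelines and regulation, so a primary claim resting on a favourable visit or outcome would matter.

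**Working it through.** **1. Reproduce the plan's figure.** Inputs from Sample size estimation: p1 = 0.20 (TC), p2 = 0.30 (Mixed), alpha 0.05, power 80%. Two-sided testing is assumed, since the sidedness is not stated. The mean proportion is 0.25.

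n = [z(1−α/2)·√(2·0.25·0.75) + z(0.80)·√(0.20·0.80 + 0.30·0.70)]² / 0.10²
= [1.960·0.6124 + 0.8416·0.6083]² / 0.01 = 293.2, so 294.

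With continuity correction: (n/4)·[1 + √(1 + 4/(n·0.10))]² = (293.2/4)·[1 + √1.1364]² = 312.8, so **313**. This matches exactly. The sizing is therefore one pairwise contrast at an undivided 0.05.

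**2. Only the 60-month tests count (two tests).**
- Independent: 1 − 0.95² = 0.0975.
- Correlated normal test statistics, |z| > 1.96: 0.098 at correlation 0, falling to about 0.070 at 0.9.
- Simulated null trials, Fisher's test for cessation and a mean-difference test for reduction, Mixed against TC, 400 evaluable per group (500 × 0.80): 0.08–0.09.
- Simulated with a three-group test for cessation plus TC against Mixed for reduction: 0.083–0.107. Each setting had 2,000 runs, so the simulation error is √(0.1·0.9/2000) ≈ 0.007.

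Overall, about 7–11%.

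**3. Any visit of either outcome can count (Mixed against TC, 2 × 5 = 10 tests).** Independent: 1 − 0.95¹⁰ = 0.401. With a common assumed correlation:

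| Correlation | 0 | 0.3 | 0.5 | 0.7 | 0.9 |
|---|---|---|---|---|---|
| At least one p<0.05 | 0.40 | 0.35 | 0.29 | 0.21 | 0.13 |

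The simulation of Fisher and mean-difference tests gave 0.31, 0.26 and 0.19 for latent within-person correlations of 0.5, 0.7 and 0.9. It assumed abstinence of 5, 8, 12, 16 and 20% at the five visits. Overall, about 13–40%.

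**4. Intermediate reading.** If cessation may count at any visit but reduction only at the end, there are six tests. Independent: 1 − 0.95⁶ = 0.265, and less with positive correlation.

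**5. Power if alpha is controlled.** With 400 evaluable per group, power for cessation is Φ[(0.10·√400 − z·0.6124)/0.6083]. With continuity correction, 0.10 is replaced by 0.10 − 1/400.
- Alpha 0.05 (z = 1.960): 0.906, or 0.891 corrected.
- Alpha 0.025 (z = 2.241): 0.849, or 0.829 corrected.

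The size needed at alpha 0.025 is 375 per group, and 375/0.80 = 469 after dropout, within the planned 500. For reduction (difference 2, SD 6): 2/(6·√(2/400)) = 4.71, and Φ(4.71 − 2.24) is over 0.99.

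**The case against.** Several points on the other side are sound.

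- **Reduction is already fixed.** A reader might infer that both outcomes are tested across three groups with no deciding contrast. That is not so: outcome 2 concerns TC and Mixed only, and its contrast and visit are stated. The 5-year rates used for sizing also point to 60 months for cessation, although analysis A does not say so.
- **No single error rate follows from the text.** A reader might quote 20–30% as the plan's false positive rate. That depends on one reading of which tests count as primary and on assumed correlations. On the narrow reading the rate is about 7–11%.
- **The Cox model gives one group effect over the whole follow-up**, and mixed models for repeated observations are foreseen. This weakens the picture of five separate verdicts on cessation. But the plan does not make either model decisive, and the 0.05 rule covers the visit tests as well.
- **Early publication.** A reader might infer that early visits will be published as primary findings. The timetable calls those data preliminary and places final results in 2019, so the text does not support this.
- **EC.** The EC group does not smoke traditional cigarettes at entry, so equal abstinence is not a plausible null there, and EC contrasts should not be added to the count.
- **Cohort design and unseen SAP.** How strictly to control error in a non-randomised cohort is partly judgement. An alpha hierarchy can properly sit in a SAP, so its absence from an article is no finding. What can be assessed is the stated rule, which as worded applies 0.05 to everything.

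**Conclusion.** The point holds in a limited form. Two primary outcomes share no alpha control, and for cessation the stated primary comparison (three groups, no visit) does not match the contrast that was sized (Mixed against TC at 5 years). The chance of at least one false positive primary result is above 5% on each reading checked: about 7–11% with the 60-month tests alone, and about 13–40% if any visit counts for Mixed against TC. Both ranges assume two-sided tests and a null of no difference. The correlations are assumptions (0 to 0.9 in the normal calculation), because the document gives none. The error rates do not carry over to EC. The plan should be corrected, but the defect does not undermine the planned sample size.

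**What to change.** In Sample size estimation and Data analysis:

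- Name Mixed against TC at 60 months, the contrast that was sized, as the deciding comparison for each primary outcome.
- Hold overall alpha at 0.05 across the two outcomes. Either use Holm (smaller p-value against 0.025, then the other against 0.05), or test in fixed order with cessation first and reduction second, each at 0.05.
- Report the 6 to 36 month results and the EC comparisons as supportive, with confidence intervals.
- Limit the sentence on p<0.05 to match.

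The planned Fisher and Cox analyses can stay.

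**Cost.** No extra participants are needed. Early visits can no longer be claimed as confirmatory, and the EC part of analysis A becomes supportive, which is a change of status and not only of wording. Under Holm, unadjusted power for 20% against 30% with 400 evaluable per group falls from about 89–91% to at worst about 83–85%. In fixed order, cessation loses no power.
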